## Methods

### Study design

This protocol paper has been written in line with the standards of Standard Protocol Items: Recommendations for Interventional Trails (SPIRIT) [16]. We will perform a multicenter prospective cohort study with patients who have decided to be given a total KA (TKA) or a unicompartmental KA (UKA). To establish generalizability, the BAAS pathway will be performed in two high-volume KA hospitals in the Netherlands serving a representative population of working patients receiving KA. For the effectiveness of BAAS regarding RTW, the results of the study will be matched in pairs and compared to individual patient data on RTW by matched pairs from prospectively performed cohort studies in the Netherlands on care as usual, namely the Expect to Work cohort and the ACTIVE trial [17, 18]. For the economic evaluation, a comparison will be made with individual patient-level data using the care-as-usual group of the ACTIVE trial in the Netherlands [17]. The study has been approved by the Medical Ethical Committee of the Amsterdam UMC, location AMC (reference ID: W21_454 # 21.504) and the Medical Ethical Committees of the local hospitals Nij Smellinghe (NS, reference ID: 19,888) and Elizabeth Tweesteden Ziekenhuis (ETZ, reference ID: L1429.2021).

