### Measures

#### Primary outcomes

For the study on effectiveness, the primary outcomes are first day of RTW and/or first day of full RTW. First day of RTW is defined as: time in days from surgery to the first day of returning to work, regardless of the number of working hours or tasks performed. Full RTW is defined as: time in days from surgery to the first day a patient works the number of hours stated in his or her employment contract regardless of the tasks performed. For self-employed patients, full RTW is defined as: the first day of the week a patient works the number of hours equal to the number of hours he or she worked before surgery. For the first days to RTW the prospective Expect to Work study by Van Zaanen et al. will be used as usual care cohort, and for full RTW the ACTIVE trial comparison group by Straat et al. will be used [17, 18]. Test–retest reliability, minimal clinical importance difference, and minimal detectable difference of self-reported RTW are not described in the medical literature, if we are not mistaken. The effectiveness study of BAAS will be reported according to the Strengthening the Reporting of Observational Studies in Epidemiology (STROBE) guidelines [19].

For the economic evaluation, the primary outcomes are the total costs of the intervention, and the societal and health care cost obtained by a cost-questionnaire at 3, 6, 9 and 12 months according to the guidelines of the Dutch Health Care Institute (Zorginstituut Nederland), in line with the study performed by Straat et al. [17, 20]. The economic evaluation will be reported according to the Consolidated Health Economic Reporting Standards 2022 (CHEERS 2022) and we will use the human-capital method [21].

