Costs of the BAAS care pathway intervention include: (i) cost of case managers; (ii) cost of compiling the report by the OCM; (iii) cost of professionals present at the digital interdisciplinary consultation and (iv) cost of the use of the accelerometer program. These costs will be estimated using the micro-costing approach. In other words, the cost estimation will be based on actual resources depleted, which will be assessed using prospective data collection, and will be valued in accordance with the Dutch guidelines for conducting economic evaluations in health care [20]. Societal cost includes occupational health care services, informal care, unpaid productivity loss, absenteeism, presenteeism and other health care services. Absenteeism (e.g. total number of sick leave days, measured prospectively by the MCM) and presenteeism (e.g. lower productivity as compared to normal while at work) will be valued using sex-specific price weights [20]. Unpaid productivity losses (e.g. voluntary work) and informal care are measured by asking the number of hours per week patients were unable to perform unpaid activities in the cost-questionnaire. Unpaid productivity losses and informal care will be valued using a recommended Dutch shadow price [20]. Using consumer price indices, all costs will be converted to the same reference year by using the human-capital method.

For health care costs, all costs according to the formal Dutch health care sector will be obtained, including cost of primary care (e.g. family physician or primary care physical therapist), secondary care (e.g. hospital stays and visits), tertiary care (vocational rehabilitation) and medication. If available, these will be valued using Dutch standard costs [20]. If unavailable, prices of professional health care organizations will be used. Medication use will be valued using prices derived from http://www.medicijnkosten.nl. All costs will be summed and divided by the number of participants, separate for both groups. This will lead to average (95% CI) total costs per participant.

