### Data collection

For the effectiveness study, both date of surgery and RTW data are collected by the MCM. In addition to the RTW data, the preoperative data and health surveillance data (Fig. 1) are collected in the same file by the same MCM.

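### The article names two sources for absenteeism in BAAS, a cost questionnaire and the medical case manager, so sick leave may be measured differently from the ACTIVE comparison group

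*Protocol article*

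**What the plan says.** The economic comparator is external. Under Study design, "a comparison will be made with individual patient-level data using the care-as-usual group of the ACTIVE trial in the Netherlands".

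Under Primary outcomes, the economic outcomes include "the societal and health care cost obtained by a cost-questionnaire at 3, 6, 9 and 12 months". The same sentence describes this as aligned with the Dutch costing guideline and with the study that supplies the ACTIVE comparison group.

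The costing paragraph that follows defines the components: "Societal cost includes occupational health care services, informal care, unpaid productivity loss, absenteeism, presenteeism and other health care services". It then gives absenteeism its own source: "Absenteeism (e.g. total number of sick leave days, measured prospectively by the MCM". Unpaid productivity loss and informal care are assigned to the cost questionnaire.

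The case manager belongs to the intervention: "Costs of the BAAS care pathway intervention include: (i) cost of case managers". Under Data collection, for the BAAS effectiveness study, "both date of surgery and RTW data are collected by the MCM".

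Under Statistical methods, Economic evaluation, the cost difference is analysed by ordinary least squares with bootstrapping, with propensity matching on patient, surgical and job characteristics. A difference counts as relevant when BAAS brings more financial benefit than usual care. No minimum amount is set.

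**The concern.** Absenteeism is the cost component a return-to-work pathway is most directly meant to reduce, so its measurement matters more than that of most other items. The article gives it two sources. One is a questionnaire that could exist in both cohorts. The other is a record made by a professional who, on this article's description, works only in BAAS.

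If the second source values absenteeism in BAAS while ACTIVE relies on something else, part of the cost difference could come from how sick leave was captured. At stake is a primary economic outcome, under a decision rule in which the sign of the difference is enough.

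**Working it through.** The plan states no figure that can be reproduced here, so the check sets the statements side by side.

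**Step 1: is absenteeism covered by the questionnaire statement?** Yes. The outcome statement takes societal cost from the questionnaire, and the component list includes absenteeism as a societal cost.

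**Step 2: does the component text name another source?** It says the MCM measures sick-leave days prospectively. The same paragraph names the questionnaire for unpaid productivity loss and informal care. It therefore assigns sources item by item, and absenteeism receives a different one. Secondary measures adds the iPCQ, a productivity-cost questionnaire, without saying whether it or the MCM record values absenteeism.

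**Step 3: can the MCM source exist in both cohorts?** The MCM delivers BAAS and is costed as part of it. The comparator is an existing usual-care group. Nothing in the article gives those patients an equivalent record.

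**Step 4: can the analysis correct a difference in source?** Let D be true sick-leave days, e the recording error of the source, and p the price per day. For matched patients the recorded difference in absenteeism cost is

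p × [(D_BAAS + e_BAAS) − (D_ACTIVE + e_ACTIVE)] = p × (D_BAAS − D_ACTIVE) + p × (e_BAAS − e_ACTIVE).

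The listed matching factors are UKA versus TKA, gender, BMI, physical nature of the job, preoperative sick leave and work-relatedness of symptoms. They act on the first term, by making patients comparable. They do not touch the second. Bootstrapping describes sampling variation and does not touch it either. With the same instrument, recall period and window in both cohorts, and similar error behaviour (an assumption), e_BAAS ≈ e_ACTIVE and the second term largely cancels.

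**Step 5: does the decision rule absorb a small artefact?** No. Without a margin, the second term changes the conclusion whenever it is opposite in sign to the true total cost difference and larger than it in absolute size. If the true difference is near zero, a small artefact is enough.

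**Step 6: is the observation window the same?** The Table 1 footnote says marked follow-up measurements stop after full return to work, and Study intervention makes full return to work a stop criterion for the pathway. If sick-leave collection in BAAS stops there while the ACTIVE data run to 12 months, later absence spells would be missed in BAAS only, which would favour BAAS. The table body is not readable in the text at hand, so whether a cost measure carries the mark cannot be determined.

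**Step 7: can the error term be sized?** No. The documents give no error rate for either source and do not describe ACTIVE's sick-leave instrument.

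**The case against.** The strongest reply is that the two statements are compatible. A questionnaire is an instrument; the MCM is a person who collects data. Study intervention has patients fill in questionnaires, including the iPCQ, at the MCM's preoperative examination, and Data collection has the MCM keep the data in one file. The phrase could mean only that the MCM administers the questionnaire. This stands as a possible reading. The article does not state it, however, and the item-by-item assignment of sources points the other way.

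A second reply is that ACTIVE's method is not described. That is correct. A reader might infer that the article shows ACTIVE to have used periodic patient recall, and so that a bias is demonstrated. The documents do not support this: the only link is a remark that the costing follows the comparator study, in a sentence that also covers the guideline and the time points. ACTIVE could have registered sick leave prospectively by other means.

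A reader might also apply an assumed recording error to the feasibility study's 12.4 weeks to full return to work and quote a bias in days. That is not supported. No error rate is documented. Time to full return overstates absence, because first return in the same study averaged 6.4 weeks and partial work fills part of the interval. The one-week relevance threshold belongs to the effectiveness outcome, not to costs.

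Finally, mapping cost items to instruments can be left to a fuller document. That would excuse silence, but the article names two sources for one item.

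**Conclusion.** The point holds as a conditional one. The article gives two sources for a component of a primary economic outcome, and one of them is specific to BAAS. If the MCM record values absenteeism in BAAS, the comparison with ACTIVE may mix a difference in measurement with a difference in sick leave. The planned model and matching do not correct that, and the cost rule leaves no room for it.

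The conclusion assumes that the MCM record is separate from the questionnaire and that ACTIVE used another source. Neither is settled by the article. Direction and size are unknown, and no estimate in days or money should be attached. The issue is confined to absenteeism: unpaid productivity loss and informal care are explicitly assigned to the questionnaire. It merits correction before the cost analysis because the item is central and the repair is small.

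**What to change.** Make the outcome statement and the costing paragraph under Primary outcomes agree on where sick-leave days come from, and state how ACTIVE recorded them. If the MCM only administers the questionnaire, say so.

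In the primary economic comparison, value absenteeism from the instrument, recall period and 12-month window available in both cohorts: the cost questionnaire, if the ACTIVE data hold it. Confirm that this collection continues after full return to work, given the Table 1 footnote.

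Use the MCM-recorded days as a sensitivity analysis, and report their agreement with the questionnaire within BAAS.

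The cost is a short clarification and one further analysis. There is a real downside. The questionnaire may be less precise than the MCM record, and the article itself says the test–retest reliability of the iPCQ is unknown. Waves not completed cannot be recovered and would need imputation, which the plan already foresees for missing cost data.

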#### Secondary measures

The Work, Osteoarthritis and Joint-Replacement Questionnaire (WORQ) is a questionnaire containing thirteen 0–4-scale questions regarding perceived difficulty with performing work-related knee straining activities, calculated to a 0–100 total score, in which a higher score represents less difficulties performing the activity [22]. The WORQ is a reliable, valid, and responsive questionnaire that can be used to evaluate the impact of knee complaints following KA on patients' ability to work with an inter rater correlation (ICC) of 0.97 [22].

The Knee Injury and Osteoarthritis Outcome Score (KOOS) is a questionnaire containing thirty-seven 0–4 ordered category questions regarding KA-related symptoms, pain, activities, sport participation, and quality of life domains, normalized into a 0–100 total score on every domain, in which a higher score represents less restriction on the given domain [23, 24]. The KOOS demonstrates adequate content validity, internal consistency, test–retest reliability, and construct validity with an ICC of 0.85—0.90 [25].

The Central Sensitization Inventory (CSI) is a questionnaire containing twenty-five 0–4-scale questions regarding pain sensitization-related symptoms in which a higher score represents a higher change on pain sensitization-related symptoms [26]. The Dutch translation of the CSI has four distinguishable domains, has good internal consistency for the total score and three out of four domains, good discriminative power, and excellent test–retest reliability [26].

The Work Ability Score (WAS) consists of the worker’s self-reported current work ability compared to the lifetime best. The score ranges from 0 to 10 and a lower score represents a lower ability to work [27]. The WAS is more user-friendly than the Work Ability Index and has a good and comparable reliability [28].

The iMTA Productivity Cost Questionnaire (iPCQ) is a questionnaire containing cost-related questions regarding health and work [29, 30]. Test–retest reliability, minimal clinical importance difference, and minimal detectable difference of the iPCQ are unknown.

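### Informal care is given a measure that records the patient's own lost unpaid activity, so as written this part of the societal cost is not validly measured

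*Protocol article*

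**What the plan says.** Four statements in the Primary outcomes section of the protocol article bear on this point.

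- **Source.** Among the primary economic outcomes, alongside what the pathway itself costs, is "the societal and health care cost obtained by a cost-questionnaire at 3, 6, 9 and 12 months".
- **Components.** "Societal cost includes occupational health care services, informal care, unpaid productivity loss, absenteeism, presenteeism and other health care services". Informal care and unpaid productivity loss appear here under separate names.
- **Measure.** A single sentence covers both. Its subject is unpaid productivity losses, with voluntary work as the example, together with informal care. It continues: "informal care are measured by asking the number of hours per week patients were unable to perform unpaid activities in the cost-questionnaire".
- **Valuation and total.** "Unpaid productivity losses and informal care will be valued using a recommended Dutch shadow price", and later "All costs will be summed and divided by the number of participants, separate for both groups".

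The only other cost instrument described is the iPCQ, under Secondary measures. The article says that it "is a questionnaire containing cost-related questions regarding health and work" and mentions no item on help received. The Economic evaluation section then compares the BAAS cohort with the usual-care group of the ACTIVE trial by ordinary least squares regression with bootstrapping.

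**The concern.** Informal care, as a cost to society, is the time that relatives, friends or others spend helping the patient. Unpaid productivity loss is the time the patient could not spend on his or her own unpaid tasks. These are hours of different people, and a patient can have many of one and few of the other. The stated question asks only about the second, yet the article uses it for both.

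This is more than a detail left out of a condensed article. The article does say how informal care is measured, and the quantity it names is the wrong one.

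The stake is a primary outcome. The Economic evaluation section sets no margin: a difference counts as relevant as soon as the intervention comes out financially better than usual care. The sign of the cost difference therefore carries the conclusion, and an error in a component feeds straight into it.

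**Working it through.** The article states no hours, no shadow price and no cost figure, so there is no figure to reproduce. The check is an accounting one, in symbols.

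**Inputs**
- h = hours per week the patient could not perform unpaid activities (the stated question, Primary outcomes).
- c = hours per week of unpaid help the patient received (no source described in the article).
- p = shadow price per hour (named in Primary outcomes, amount not given). One price is assumed for both components, since the article names one.

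**Step 1: what the two component names call for.** Unpaid productivity loss plus informal care = hp + cp.

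**Step 2: the text applied with each listed component valued and summed.** Both are measured by h, so the sum is hp + hp = 2hp. The error per patient-week is 2hp − (hp + cp) = (h − c)p. It is positive when h exceeds c, negative when c exceeds h, and zero only if the two happen to be equal. If the prices differed, the same subtraction gives (h − c) times the price used for informal care.

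**Step 3: the text applied as one combined item valued once.** The sum is hp. The error is hp − (hp + cp) = −cp. Nothing is counted twice, but help received is absent although the component carries its name.

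**Step 4: the comparison with ACTIVE.** Write Δ for the mean difference between the groups, and assume both groups are scored by the same rule.

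| Reading | Error in the cost difference | Vanishes when |
|---|---|---|
| Two components, each valued | (Δh − Δc)p | Δh = Δc |
| One combined item | −Δc · p | Δc = 0 |

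Under either reading c has no data source in the article. That part of the finding does not depend on how the sentence is read. The double count arises only in Step 2.

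**The case against.** The strongest reply has three parts.

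**The double count is inferred.** The article describes one question and one shadow price for the two items taken together. That can well mean a single combined item valued once. The component list says what societal cost covers, not that each name is a separately computed line. This stands. A reader might infer that the plan doubles any between-group difference in lost unpaid hours, but the text does not establish that. It is one possible reading, and no percentage can be attached to it without inventing hours.

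**Informal care may mean care the patient could no longer give to others.** Giving care is an unpaid activity, so the question would then fit both terms. The text does not say this. On that reading such care already lies inside h, so it must not be added again, and help received by the patient is still outside the total.

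**The questionnaire is not shown.** The article says costs follow the Dutch Health Care Institute guidelines and are in line with the ACTIVE study, and one sentence may compress two separate items. This also stands in part. A reader might infer that help received was never collected, but the documents cannot show that. The fault is in the measurement as described, not demonstrably in the data.

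None of this makes the stated question a measure of help received.

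**Conclusion.** The point holds in a limited form. As the article is written, informal care is not validly measured: the named quantity is the patient's own lost unpaid activity, and no other item on help received is described. If the two listed components are each valued and summed, the same hours are also counted twice, with an error of (h − c)p per patient-week. If they form one item valued once, there is no double count and the shortfall is cp.

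The size and direction in euros are unknown, because the article gives neither hours nor a price. Nor does it show whether lost unpaid hours and help received would move together or apart under the pathway. The algebra assumes one shadow price for both components and, for the group comparison, the same scoring in both cohorts. Because societal cost is a primary economic outcome, the definition should be corrected before the costs are compared.

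**What to change.** 1. Use the hours unable to perform unpaid activities for unpaid productivity loss only, and state that these hours enter the total once.
2. Define informal care as hours per week of unpaid help received from family, friends or others. Take it from its own item, provided that the BAAS cost-questionnaire and the ACTIVE data both contain a comparable one.
3. If either lacks such an item, remove informal care from the societal total that is compared between the groups, and say so in the methods and the report.

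Adding a new question now is not a full solution. It cannot be added to ACTIVE data already collected, and introducing it in BAAS part-way would leave informal care measured differently across patients and time points.

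The cost is a few sentences and a check of two questionnaires. The downside is that the compared societal total may exclude informal care, so it would be narrower than the component list now promises.

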#### Secondary measures

The Work, Osteoarthritis and Joint-Replacement Questionnaire (WORQ) is a questionnaire containing thirteen 0–4-scale questions regarding perceived difficulty with performing work-related knee straining activities, calculated to a 0–100 total score, in which a higher score represents less difficulties performing the activity [22]. The WORQ is a reliable, valid, and responsive questionnaire that can be used to evaluate the impact of knee complaints following KA on patients' ability to work with an inter rater correlation (ICC) of 0.97 [22].

The Knee Injury and Osteoarthritis Outcome Score (KOOS) is a questionnaire containing thirty-seven 0–4 ordered category questions regarding KA-related symptoms, pain, activities, sport participation, and quality of life domains, normalized into a 0–100 total score on every domain, in which a higher score represents less restriction on the given domain [23, 24]. The KOOS demonstrates adequate content validity, internal consistency, test–retest reliability, and construct validity with an ICC of 0.85—0.90 [25].

The Central Sensitization Inventory (CSI) is a questionnaire containing twenty-five 0–4-scale questions regarding pain sensitization-related symptoms in which a higher score represents a higher change on pain sensitization-related symptoms [26]. The Dutch translation of the CSI has four distinguishable domains, has good internal consistency for the total score and three out of four domains, good discriminative power, and excellent test–retest reliability [26].

The Work Ability Score (WAS) consists of the worker’s self-reported current work ability compared to the lifetime best. The score ranges from 0 to 10 and a lower score represents a lower ability to work [27]. The WAS is more user-friendly than the Work Ability Index and has a good and comparable reliability [28].

The iMTA Productivity Cost Questionnaire (iPCQ) is a questionnaire containing cost-related questions regarding health and work [29, 30]. Test–retest reliability, minimal clinical importance difference, and minimal detectable difference of the iPCQ are unknown.

The de Morton Mobility Index (DEMMI) is a 15-item unidimensional mobility instrument that measures static and dynamic balance. The 15 items are recalculated to a 0–100 points score, in which a higher score represents better mobility [31]. The DEMMI has a good validity, a Minimal Detectable Change (90; MDC), and minimal clinical important difference (MCID) of respectively 9 and 10 points [31].

The 6MWT is a walk test in which the maximum walking distance is measured during a period of six minutes [32]. The 6MWT has an MCID of 74.3 m [33].

The 30-STST is an instrument to assess the functional status of patients. A patient is asked to perform as many sit and stand repetitions within 30 s without using their hands. The 30-STST is a valid and reliable instrument and has an MCID of 1.13 [34].

The FTST is a similar test to the 30-STST and measures the time it takes for a patient to perform 5 sit and stand repetitions without using their hands. Because of their similarity, the 30-STST and FTST can be performed simultaneously. The FTST is a valid and reliable instrument and has an MCID of 2.3 s [35].

The floor-to-waist lifting test is a reliable and valid performance-based test to assess a patient’s functional capacity [36, 37]. Reference values to assess whether a patient is restricted regarding functional capacity to RTW are between 16 and 24, dependent on the physical nature of the job [38].

